### Sample size

This study will include *N* = 70 adolescents (35/35) in order to explore the impact of smartphone-augmented CBT on therapy homework adherence among adolescents with depressive and anxiety disorders. Based on a recent systematic review [49], which analyzed the effects of adjunctive apps on therapy across 19 studies, the sample size of 70 in our study lies within the range of reported sample sizes, thus providing a solid basis for comparing the efficacy of adjunctive mobile applications in therapeutic settings. Additionally, a study employing a comparable methodology, which involves a comparison of two groups of 35 participants over four evaluation periods (including before treatment, after treatment, and follow-up assessments), anticipates moderate impacts of their app specifically on therapy homework adherence. For the comparison between groups across four measurement time points, a power analysis indicated a power of 0.84 with a sample size of 35 per group (app vs. no app) at an α level of 0.5 [66]. Additionally, the statistical power of a sample can be enhanced through a large number of observations per participant [34, 92]. In our research, THA will be evaluated for a minimum of three homework tasks per week over approximately 16 weeks.

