#### Analyses of secondary endpoints

For the secondary outcomes, we will conduct analyses utilising either mixed models for repeated measures, employing a heterogeneous first-order autoregressive structured covariance matrix over time, or generalized estimating equation approaches with corresponding marginal means and contrast tests (multilevel modelling). Time-to-dropout distributions will be summarised using the Kaplan-Meier method and compared using the (stratified) log-rank test. Efficacy variables will be summarised by time point and treatment arm, including mean, standard deviation, percentiles (minimum, 25th, 50th, 75th, and maximum), count, and percentage. Additionally, moderation, mediation, and conditional process modelling will be performed based on regression and structural equations (interaction, simple slope analysis; direct/indirect effects, kappa squared).

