#### Mediators of change

Potential mediators that will be analyzed include (1) treatment fidelity as assessed by the therapist using an integrity questionnaire after each session. Therapists will document the interventions and treatment manuals that were used as well as the therapy homework the patient has to complete before the next session. (2) Additional potential mediators that will be analyzed are health-related quality of life, self-perception profiles, and emotion regulation strategies measured using the self-report KINDL^R^, Harter scale, and FEEL-KJ, respectively (see above). (3) Furthermore, treatment adherence assessed following each therapy session will be evaluated as a mediating factor using the Adherence Questionnaire (see above). This assessment will include four distinct items to define adherence, focusing on the patient’s engagement during the therapy sessions. Moreover, for each therapy-related homework task that the patient is given to complete before a session, execution adherence will be assessed after the session.

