### Missing data

It is important to minimize treatment discontinuation among patients and ensure that all patients are followed up and documented after treatment discontinuation in order to collect the data according to the intention-to-treat (ITT) principle. Multiple imputation approaches will be employed to evaluate the potential impact of up to 20% attrition, considering proxy measures and assuming specific patterns of missingness not at random. These details will be documented in a statistical analysis plan. Additionally, supporting evidence will be provided by analyzing subjects who are essentially observed and treated per protocol.

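### Kappa squared is fixed as the mediation effect size, but its denominator is not an attainable maximum and its estimate is unsigned and biased upward (minor)

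*Protocol article*

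**What the plan says.** Under Analyses of secondary endpoints the protocol states that "moderation, mediation, and conditional process modelling will be performed based on regression and structural equations", and the bracket after it lists "direct/indirect effects, kappa squared". No other effect size for mediation is named, and kappa squared is neither defined nor qualified.

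The section Mediators of change lists the candidates: "Potential mediators that will be analyzed include (1) treatment fidelity"; then "Additional potential mediators that will be analyzed are health-related quality of life, self-perception profiles, and emotion regulation strategies"; then "treatment adherence assessed following each therapy session will be evaluated as a mediating factor using the Adherence Questionnaire". The index would therefore be reported for several mediators. The Discussion also names homework adherence as a possible mediator of the app's effect on treatment outcomes.

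The sample is 70 adolescents, 35 per arm (Sample size). The Missing data section plans to "evaluate the potential impact of up to 20% attrition".

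**The concern.** Kappa squared is meant to be read as the indirect effect relative to the largest indirect effect that the data would allow. If no such largest value exists, that reading is invalid, whatever the number turns out to be.

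Two further properties matter in a trial of 70. The bounds in the denominator take the signs of the estimated paths, so the ratio cannot be negative. A mediator that the app lowers and one that it raises by the same amount get the same value. And because sampling error cannot pull the estimate below zero, it sits above zero on average even when the app does not affect the mediator. At stake is how the size of the proposed mechanism is described for each listed mediator. The primary endpoint is not affected.

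**Working it through.** **Inputs.** From the protocol: 35 + 35 patients; up to 20% attrition, so 70 × 0.80 = 56 analysed. The protocol gives no path values, no definition of kappa squared and no figure to reproduce. The standard definition and the standardised paths below are assumptions: a is group to mediator, b is mediator to outcome given group, and X, M, Y are group, mediator and outcome.

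**Definition.** κ² = ab / [M(a)·M(b)], with
- M(a) = r_MY·r_XY ± √(1 − r_MY²)·√(1 − r_XY²)
- M(b) = ± √(1 − r_XY²) / √(1 − r_XM²)

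where the signs follow the estimated a and b.

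**1. Is there a maximum of ab?** A 3 × 3 correlation matrix with r_XM = a and r_XY fixed is valid as long as |b| ≤ √(1 − r_XY²)/√(1 − a²). So ab can reach a·√(1 − r_XY²)/√(1 − a²). At r_XY = 0.2:

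| a | bound on ab |
|---|---|
| 0.5 | 0.57 |
| 0.9 | 2.02 |
| 0.99 | 6.88 |
| 0.999 | 21.9 |

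The bound grows without limit as a approaches 1. Positive definite matrices at 95% of the bound on b exist (a = 0.99: b = 6.60, ab = 6.53).

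**2. What the denominator is instead.** Take a = b = 0.3 with no direct effect, so r_XY = 0.09 and r_MY = 0.3.
- M(a) = 0.3 × 0.09 + √0.91 × √0.9919 = 0.977
- M(b) = √0.9919/√0.91 = 1.044
- product 1.020, so κ² = 0.09/1.020 = 0.088

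M(a) is found with r_MY held fixed and M(b) with r_XM held fixed, and the two do not hold together. At a = 0.977 with r_MY = 0.3 and r_XY = 0.09, b would be (0.3 − 0.977 × 0.09)/(1 − 0.977²) ≈ 4.7, not 1.044. The product is not the maximum of ab.

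**3. Sign.** With b = 0.3 and no direct effect, a = +0.3 and a = −0.3 both give κ² = 0.088, while ab is +0.09 and −0.09.

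**4. No app effect on the mediator (a = 0).** 20,000 simulated trials per setting:

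| n | b | mean ab | mean \|ab\| | mean κ² | 95th percentile of κ² |
|---|---|---|---|---|---|
| 70 | 0 | 0.000 | 0.009 | 0.010 | 0.03 |
| 70 | 0.3 | 0.000 | 0.029 | 0.030 | 0.08 |
| 70 | 0.5 | 0.000 | 0.048 | 0.054 | 0.13 to 0.14 |
| 56 | 0 | 0.000 | 0.012 | 0.012 | 0.04 |
| 56 | 0.3 | 0.000 | 0.032 | 0.034 | 0.10 |
| 56 | 0.5 | 0.000 | 0.053 | 0.060 | 0.15 |

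The estimate was above zero in every simulated trial. The population value is exactly 0 when ab = 0.

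**5. Behaviour at plausible effects.** With two equal arms, a group difference of d standard deviations in the mediator gives a = d/√(d² + 4). No direct effect assumed:

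| d | a | b | ab | κ² |
|---|---|---|---|---|
| 0.5 | 0.24 | 0.3 | 0.073 | 0.073 |
| 0.5 | 0.24 | 0.5 | 0.121 | 0.129 |
| 1.0 | 0.45 | 0.3 | 0.134 | 0.123 |
| 1.0 | 0.45 | 0.5 | 0.224 | 0.215 |

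κ² peaks at a of about 0.71 to 0.72 (d of about 2.0 to 2.1) and then falls while ab rises. With b = 0.5 it goes from 0.27 at a = 0.7 (ab = 0.35) to 0.17 at a = 0.95 (ab = 0.475), where d is about 6.1.

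**The case against.** The case for leaving the text alone is that the consequences are slight, and most of it stands.

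- The sign is not lost to the reader: signed direct and indirect effects are to be reported beside kappa squared.
- The unbounded ab and the reversal show up only at very large group differences. For a difference of 0.5 to 1.0 standard deviations, kappa squared is within about 0.01 of ab.
- The positive average under no mediation is mostly what any unsigned estimate does. Mean |ab| is 0.009 to 0.048 against 0.010 to 0.054 for kappa squared, so the contrast with the mean of signed ab overstates what is peculiar to the index.
- Mediation is supplementary, and neither the sample size nor a stopping decision rests on it.

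A reader might infer that the trial will claim mediation for every listed mediator, or will report a misleading share of the effect that is mediated. The protocol supports neither. It does not say that a positive kappa squared will be taken as evidence, it promises no proportion mediated, and kappa squared is not one. Nor can the pilot be used to show that the app lowers a mediator. The Discussion reports that adherence to therapy and research protocol fell in the pilot, but also that three therapist sessions were added in response, and it gives no estimated effect.

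What the objection does not answer is that the protocol fixes a particular statistic whose intended meaning is invalid, and which adds nothing valid to the indirect effect already planned.

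**Conclusion.** The point holds at minor severity. Kappa squared cannot be read as a proportion of a maximum indirect effect, because with the group–outcome correlation fixed there is no finite maximum. This follows from algebra and needs no assumed path values. At 35 + 35 with no app effect on the mediator, its estimate averages about 0.01 to 0.05 where the population value is 0. That range rests on the standard definition and on assumed b of 0 to 0.5, and an unsigned ab would behave much the same. The reversal with rising ab needs group differences of about 2 standard deviations or more. The harm is confined to the effect-size statement in a supplementary analysis; the planned estimates of the direct and indirect effects are unaffected.

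**What to change.** In Analyses of secondary endpoints, delete kappa squared. As the effect size, report the signed indirect effect divided by the outcome standard deviation (partially standardised, which suits a two-level treatment), beside the raw indirect effect in points of the outcome scale, with a percentile bootstrap confidence interval.

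The cost is a few words in the analysis section. No data, visits or design changes are needed. The change should be fixed before outcome data are analysed.

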### Interim analyses

Interim analyses will be conducted with *N* = 18 patients per group to decide upon the continuation of the trial. If results are contrary to expectations, the PI will make a final decision regarding termination of the trial.

### Additional analyses

#### Patient demographics/other baseline characteristics

Demographic and baseline data will be collected at T0 and summarized descriptively for all documented patients. Continuous data will be summarized using measures such as arithmetic mean, standard deviation, minimum, 25th percentile, median, 75th percentile, maximum, and the number of complete and missing observations. If applicable, continuous variables may also be presented in a categorized form. Categorical data will be summarized according to the total number of patients in each category and the number of missing values. Relative frequencies will be expressed as valid percentages (number of patients divided by the number of patients with non-missing values).

#### Predictors/moderators of treatment outcome regarding anxiety and depressive symptoms

The following variables will be evaluated as potential moderators or predictors of treatment outcomes for internalizing symptoms at T3: (1) sociodemographic variables (e.g., number of children in the family; socioeconomic status and place of residence; caregivers’ age, education, income, and occupation), which will be assessed through a caregiver questionnaire at T0, (2) severity of comorbid symptoms using the self-report YSR/11-18R and the caregiver-report CBCL/6-18R at T0 and T3 (see above), (3) patients’ specific psychological characteristics, such as intelligence, measured at T0 using the CFT20-R (see above).

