The following hypotheses will be investigated:The experimental group (CBT + JAY) will show a significantly higher overall THA score compared to the active control group (CBT) throughout the intervention phases, as assessed by quantitative aspects of therapy homework (relative ratio of completed and required entries) as well as qualitative aspects which together as a composite score constitute the primary outcome. The qualitative aspects (content fit, thoroughness, competence of behaviour/thoughts, and clinical relevance) will be evaluated by multiple independent raters using a rating system that defines the assessment criteria.The experimental group (CBT + JAY) will show higher THA compared to the active control group (CBT) as assessed using the clinician-rated Questionnaire for Therapy Adherence after each therapy session [68].The experimental group (CBT + JAY) will show a greater reduction in internalizing symptoms compared to the active control group (CBT) according to self-rating, as measured using the Internalizing Problems scale of the Youth Self-Report 11–18 (YSR/11-18R) [69, 70] as well as the self-report symptom checklists for anxiety (SCL-AD-S) and depression (SCL-DEP-S) from the “Diagnostic system for mental disorders based on ICD-10/DSM-5 for children and adolescents” (DISYPS-III) [71] and using an individual problem list.The experimental group (CBT + JAY) will show a greater reduction in internalizing symptoms compared to the active control group (CBT) according to caregiver rating, as measured using the Internalizing Problems scale of the caregiver-report Child Behaviour Checklist (CBCL/6-18R) [69, 70] as well as the caregiver-report scales for anxiety (SCL-AD-P) and depression (SCL-DEP-P) from the DISYPS-III [71].The experimental group (CBT + JAY) will show a greater reduction in internalizing symptoms compared to the active-control group (CBT) according to clinical rating, as assessed by a clinician using a structured clinical interview (ILF-INTERNAL) from the DISYPS-III [72].The experimental group (CBT + JAY) will show a stronger reduction in comorbid symptoms as measured using the scales Externalizing Problems and Total Problems of the self-report YSR/11-18R and the caregiver-report CBCL/6-18R [69, 70].Patients in the experimental group (CBT + JAY) will show a greater improvement in quality of life, sense of global self-worth, and emotion regulation strategies according to self-report compared to patients in the control group (CBT), as assessed by the Revised Questionnaire for Health-Related Quality of Life Assessment in Children (KINDL^R^) [73], by a modified German version of the Self-Perception Profile for Children called the Harter scale [74, 75], and by a modified version of the Questionnaire to Assess Children’s and Adolescents’ Emotion Regulation Strategies (FEEL-KJ) [76], respectively.Patients in the experimental group (CBT + JAY) will show greater treatment satisfaction than those in the control group (CBT), as measured by a modified version of the self-report Client Satisfaction Questionnaire (ZUF-8-M patient) [77, 78].

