#### Secondary outcomes

Secondary outcomes include:The quantity of therapy homework, as assessed by the relative ratio of completed to requested entries within the JAY app or on the paper-and-pencil sheets between the treatment sessions.Quality of the entries, as rated by a pool of clinicians based on the app entries or the homework sheets according to the rating system mentioned in the previous section.Patient-rated symptoms of anxiety and depression, assessed by the Internalizing Problems scale of the self-report YSR/11-18R [69, 70] as well as the self-report scales for anxiety (SCL-AD-S) and for depression (SCL-DEP-S) from the DISYPS-III [71]. Reliability and validity as well as sensitivity to change of the German version of the YSR/11-18R and the DISYPS-III scales have already been demonstrated in German samples [70, 71]. The Internalizing Problems scale of the YSR/11-18R will be assessed at every measurement time point and the SCL-AD-S and SCL-DEP-S will be assessed at T0 and T3.Caregiver-rated symptoms of anxiety and depression, assessed by the Internalizing Problems scale of the caregiver-report CBCL/6-18R [69, 70] as well as the caregiver-report scales for anxiety (SCL-AD-P) and for depression (SCL-DEP-P) from the DISYPS-III [71]. Reliability and validity as well as sensitivity to change of the German version of the CBCL and the DISYPS-III scales have already been demonstrated in German samples [70, 71]. The Internalizing Problems scale of the CBCL/6-18R will be assessed at every measurement time point, and the SCL-AD-P and SCL-DEP-P will be assessed at T0 and T3.Clinician-rated symptoms of anxiety and depression based on the ILF-INTERNAL from the DISYPS [72], assessed at T0 and T3.Individually defined problem behaviours were rated by the patients using an individual problem list (IPL) in every therapy session. The problem list allows for the assessment of four targeted issues, rated on a 5-point Likert scale, and of the burden of the problems, rated on a 10-point Likert scale. Individual problem lists have been shown to be reliable, valid, and sensitive to change [85].Patient- and caregiver-rated comorbid symptoms and overall behavioural and emotional problems, measured using the remaining scales Externalizing Problems and Total Problems of the self-report YSR/11-18R and the caregiver-report CBCL/6-18R [69, 70]. Reliability and validity as well as sensitivity to change of the German version of these scales have been demonstrated in German samples [70]. These outcomes will be measured at T0 and T3.Patients’ adherence during the weekly therapy sessions (e.g., engagement in tasks and activities) will be measured using the clinician-rated Adherence Questionnaire [68], which will be assessed after every therapy session. This was adapted from the AUTHARK trial [41], in which good internal consistencies were reported.Quality of life, assessed using the Revised Questionnaire for Health-Related Quality of Life Assessment in Children and Adolescents (KINDL^R^) [73], which evaluates aspects related to physical and psychological well-being, the adolescent’s self-worth, as well as friendships and family relationships. Reliability and validity as well as sensitivity to change of scale have been demonstrated in German samples [86, 87]. This outcome will be assessed at T0 and T3. Sense of global self-worth, assessed using a modified German version of the Self-Perception Profile for Children, called the Harter scale [74, 75], which evaluates perceptions of cognitive and physical competence, peer acceptance, physical appearance, and self-worth. Reliability and validity of the original scale were demonstrated in a German clinical sample [88]. This outcome will be assessed at T0 and T3. Emotion regulation strategies were assessed using a modified version of the Questionnaire to Assess Children’s and Adolescents’ Emotion Regulation Strategies (FEEL-KJ) [76], which evaluates adaptive and maladaptive strategies to regulate feelings of anxiety and sadness. Reliability and validity have been demonstrated [76]. This outcome will be assessed at T0 and T3. Retrospective mood assessments will be conducted in every week in which the patient has used the momentary assessment of the JAY app or the paper-and-pencil equivalent. All 16 momentary affective and mental states assessed during the week will be rated retrospectively for the same week on a scale from 0 to 100. Patient-rated satisfaction with the treatment, assessed using a modified version of the self-report Client Satisfaction Questionnaire (ZUF-8-M patient) [77, 78], which has been shown to be reliable, valid, and sensitive to change [89]. Satisfaction will be assessed once, at T3. Patient-rated usability of the JAY app, assessed using a German translation of the System Usability Scale (SUS), which has been shown to be reliable, usable, and valid [90]. The scale measures effectiveness, efficiency, and satisfaction of and with a system. Usability will be assessed for patients in the experimental group once, at T3. Life events in the domains of school, family, and friendships as well as illness, accidents, and losses, as measured by the Zurich Life-Event List (ZLEL), which has been shown to be reliable and valid [91]. This measure will be applied once, at the follow-up (T5) in this study.

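### Comorbid severity at T3 is listed as a moderator or predictor of internalizing symptoms at T3, and three candidate mediators have T3 as their only post-baseline value

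*Protocol article*

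**What the plan says.** The section *Predictors/moderators of treatment outcome regarding anxiety and depressive symptoms* sets out to examine "potential moderators or predictors of treatment outcomes for internalizing symptoms at T3". Its second group of variables is "severity of comorbid symptoms using the self-report YSR/11-18R and the caregiver-report CBCL/6-18R at T0 and T3". The sociodemographic variables and intelligence, listed beside it, are taken at T0 only.

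The same comorbidity scores are outcomes elsewhere. A hypothesis in *Background* states that the app group "will show a stronger reduction in comorbid symptoms as measured using the scales Externalizing Problems and Total Problems". *Secondary outcomes* lists "comorbid symptoms and overall behavioural and emotional problems, measured using the remaining scales Externalizing Problems and Total Problems", taken at T0 and T3.

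*Mediators of change* names session-wise treatment fidelity and session-wise adherence, and then continues: "Additional potential mediators that will be analyzed are health-related quality of life, self-perception profiles, and emotion regulation strategies". These are the KINDL-R, the Harter scale and the FEEL-KJ. *Secondary outcomes* gives each the same schedule: "This outcome will be assessed at T0 and T3". A further hypothesis expects the app to improve all three. *Mediators of change* does not name the outcome of the mediation models.

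*Analyses of secondary endpoints* plans moderation and mediation by regression and structural equations with direct and indirect effects. It mentions no lagged model.

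**The concern.** A moderator or predictor of a treatment outcome has to be fixed before treatment can act on it. Comorbid severity at T3 is not: on the trial's own hypothesis it is partly a result of the app. Three consequences follow.

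- Its coefficient describes two scores that vary together in one assessment wave. It does not show who will do well.
- A group-by-T3-comorbidity interaction compares the arms within strata formed after randomisation. Patients with low T3 comorbidity in the app arm need not resemble those with low T3 comorbidity in the control arm.
- If the app lowers both scores, the group term in such a model no longer carries the full app effect.

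The mediation problem is one of order. A mediator must come before the outcome. With T0 and T3 as the only measurements, better quality of life at T3 may lead to fewer symptoms at T3, follow from them, or share a cause with them, and the data cannot separate these. At stake are the research question on moderators and predictors and any statement about how the app works.

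**Working it through.** The protocol gives no figure to reproduce here: it states no effect size for symptoms and no correlation. The timing comes from the text; the sizes below are illustrations.

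**Timing**

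| Variable | Role | Measured |
|---|---|---|
| Internalizing symptoms | dependent variable, T3 | YSR and CBCL Internalizing at every time point |
| YSR/CBCL comorbidity | moderator or predictor; also an outcome | T0, T3 |
| KINDL-R, Harter, FEEL-KJ | mediators; also outcomes | T0, T3 |
| Fidelity, Adherence Questionnaire | mediators | after each session |

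Only the session-wise measures yield a post-baseline value before T3.

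**Inputs.** From the protocol: 35 per arm. Assumed: app effect on T3 symptoms of 0.5 SD (also 0.3 and 0); association r between the T3 variable and T3 symptoms of 0.3, 0.5 or 0.7; correlation of T0 with T3 of 0.5; unit variances. The simulation used 4000 trials per setting and two-sided 0.05. T3 symptoms were regressed on group, T0 symptoms and the T0 covariate, with and without the T3 covariate. True mediation was zero throughout.

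**A. The app shifts both scores in parallel.** The group effect after adjustment is d_Y − r·d_M, which is 0.5 − 0.5r when both effects are 0.5 SD. The share removed is then r.

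| r | Formula | Simulated | Removed | Power (about 0.65 without the T3 covariate) | False mediation, Sobel / joint test |
|---|---|---|---|---|---|
| 0.3 | 0.35 | 0.353 | 30% | 0.37 | 25% / 44% |
| 0.5 | 0.25 | 0.250 | 50% | 0.26 | 57% / 66% |
| 0.7 | 0.15 | 0.149 | 70% | 0.15 | 64% / 65% |

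With 0.3 SD on both, the share removed is 30%, 51% and 71%.

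**B. The T3 variable follows from T3 symptoms.** Let M = rY + e. Without T0 adjustment, a = 0.5r and b = r, so indirect/total = 0.5r²/0.5 = r², or 9%, 25% and 49%. T0 adjustment leaves residual outcome variance 1 − 0.5² = 0.75, and the ratio becomes 0.75r²/(1 − 0.25r²):

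- r = 0.3: 0.0675/0.9775 = 7%
- r = 0.5: 0.1875/0.9375 = 20%
- r = 0.7: 0.3675/0.8775 = 42%

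The simulation gives 7%, 20% and 41%. False mediation is 2%, 11% and 30% by Sobel, and 6%, 17% and 32% by the joint test.

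**C. The app does not shift the T3 variable.** 0% to 1% of the effect is removed, and false mediation stays at about 5% or below. The same error rate holds if the app affects nothing.

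**D. Larger sample.** At 200 per arm, with 0.5 SD and r = 0.5, false mediation by Sobel is 100% in A and 71% in B. The cause is bias, not imprecision.

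**E. T0 covariates only.** The estimate is 0.50 for a true 0.50.

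These figures concern the group term and the indirect effect. The point about the T3 coefficient and interaction rests on reasoning, not on a calculation.

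**The case against.** Several limits are fair, and they rule out stronger readings that a reader might infer.

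- **That the trial's treatment comparisons are biased.** The text does not support this. The analyses of the primary and secondary endpoints name no T3 comorbidity covariate. The loss of effect applies only to a group term read from the moderator or predictor models.
- **That the mediation plan is necessarily T3 on T3.** *Mediators of change* names no outcome. YSR and CBCL Internalizing are also assessed at T4 and T5, where a T3 mediator would come first. An article may leave the lagged specification to an analysis plan, so this half of the point is conditional on T3 being the outcome.
- **That bias is certain, or of a known size.** It arises only if the app shifts the T3 variable. That is the trial's hypothesis, but no effect size for it is given, and the Discussion warns that the app's added effect may be hard to detect.
- **That both scores are taken on the same day.** Only the same assessment wave is documented. *Participant timeline* foresees two visits for the T3 interview, and the questionnaires are completed online.
- **That the research question on moderators would rest on post-treatment variables throughout.** Most listed variables with a stated time point are T0 values, and the session-wise mediators are sound in their timing.

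It can also be said that the mention of T3 merely repeats the assessment schedule. The sentence does not say so. It places T3 in a list of moderators and predictors, while intelligence and the sociodemographic variables carry T0 alone. That part of the point stands in full.

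**Conclusion.** The point holds for comorbid severity at T3. As written, it is a moderator or predictor of an outcome from its own wave, although the trial treats it as an effect of the app. Its coefficient or interaction cannot carry the stated meaning, whatever the size of the bias.

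For the group term in such models, the illustrated loss is 30% to 70% when the app shifts both scores by 0.5 SD with within-arm correlation 0.3 to 0.7. It is 7% to 41% when the T3 variable only follows from symptoms, and essentially nil when the app does not move that variable. All these sizes rest on assumed inputs.

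For the KINDL-R, Harter scale and FEEL-KJ the point is conditional: as mediators of T3 symptoms they cannot be shown to come first, and a spurious indirect effect is possible; as mediators of later symptoms they have the right order. These are additional analyses, so the correction is worth making but does not touch the primary result.

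**What to change.** 1. In *Predictors/moderators of treatment outcome*, delete *and T3* from the comorbidity item, so that only T0 values serve as moderators or predictors. T3 comorbidity remains an outcome.
2. In *Mediators of change*, name the outcome and its time point. For T3 symptoms, allow only mediators measured before T3 (session-wise homework adherence, the Adherence Questionnaire and fidelity), adjusted for T0 symptoms.
3. Use the T3 values of the KINDL-R, Harter scale and FEEL-KJ only as mediators of later Internalizing scores at T4 or T5, or label the T3-on-T3 analysis as association without a causal claim. A T4 model must allow for the differing meaning of T4: eight weeks after the last session for responders, after the third treatment phase for non-responders.

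The cost is a few sentences and somewhat fewer models. No additional measurement, visit or patient is needed.
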